### Adverse events

Adverse events (AE) are defined as any undesirable experience occurring to a subject during the study, whether or not considered related to the investigational product. All adverse events reported spontaneously by the subject or observed by the investigator or his staff will be recorded. Anakinra is known as a very safe drug. Side effects are mainly related to irritation at the injection site, these reactions usually wane with prolonged treatment. We have reported from our own experience with long-term use of anakinra in patients with Schnitzler syndrome that the risk for infection is not enhanced, even in this elderly group [38]. Nevertheless, the package insert warns against infectious complications in patients with underlying illness. Rarely, neutropenia develops during treatment, which is a reason to discontinue therapy.

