**Fig. 1 Fig1:**
[figure not shown]
Study-specific procedures

Study medication will be provided by the Swedish Orphan Biovitrium (Sobi) and stored at the Department of Pharmacology of the RadboudUMC. Preparation and labelling of anakinra and placebo will be done according to the current guidelines. This will be performed by the Clinical Trials Unit department of Clinical Pharmacology of the RadboudUMC. The anakinra and placebo syringes will be identical in appearance; the placebo syringes will contain a mixture of sodium citrate, sodium chloride and polysorbate. Medication is used once daily, during a period of 4 weeks. The anakinra and placebo will be provided by the main investigator. On the first study day, patients will be instructed how to self-inject the study medication, as described by others [27]. Administration takes place in the subcutaneous tissue, most often the abdomen or the thighs. During the study, patients will be advised to set their alarm clock daily at the same time to remind them to use the medication correctly. Drug adherence will be evaluated after 1 week and after completion of treatment. Patients will return all used and unused syringes after 4 weeks.

During the intervention period, use of co-medication is only allowed when used for ≤ 14 consecutive days and on the condition that there are no known interactions with anakinra. Oral contraceptives and/or paracetamol can be used without limitation. During the follow-up period, there are no limitations regarding the use of medication. All co-medication will be registered and reported afterwards.

Since the anakinra arm is difficult to blind because of local reactions at the injection site, the research physician and the principal investigator will not be informed of the side effects. After the injection instruction by the physician assistant (PA), the patient will be instructed to report adverse effects to the PA and not to the research physician. The PA will report all side effects to an independent physician. The independent physician will examine patients if needed and is mandated to stop treatment. To evaluate blinding of the treatment, patients will be asked which medication they thought they were using during the trial, after they have completed the study.

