Study visits are carried out at week 0, week 4 and, if needed, after 6 months. After 1 week, patients will be contacted by telephone to evaluate the occurrence of any problems regarding the use of medication and drug utilization will be recorded. If there are serious side effects, an additional study visit can be performed by the independent physician at any time. Between study visits, subjects will be asked to fill out web-based questionnaires up to 6 months after their first study visit (Fig. 1).

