### Outcome measures

The primary outcome measure is fatigue severity measured with the subscale fatigue severity of the Checklist of Individual Strength (CIS) at 4 weeks, the primary endpoint of the study. Scores on the CIS subscale range from 8 to 56 (8 items, 7-point Likert Scale). This questionnaire has been validated extensively in patients with chronic fatigue syndrome [33, 34]. Patients will fill out this web-based questionnaire weekly during the course of the trial and monthly during the follow-up period (Fig. 1).

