All secondary outcome measures will be assessed at baseline and directly following the intervention (Fig. 1). Only the VAS pain scale will be filled in weekly (together with the CIS) during the trial.

At 6 months, all questionnaires evaluating primary and secondary outcomes will be repeated to evaluate if the expected effects of the medication are maintained during the follow-up period of 5 months.

Other study parameters collected at baseline will include the following: demographic data, medical history, psychiatric history, serology results collected before inclusion in the study, use of medication, smoking and the use of alcohol and drugs.

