## Discussion

This study will be the first randomized placebo-controlled trial to evaluate the effect of blocking IL-1 on symptoms in patients with CFS. Earlier studies investigated cytokine production to be of relevance in CFS patients, but conflicting results have been published [11, 13]. A possible explanation is that good controls have not been used in these studies, and cytokines were measured in peripheral blood instead of in tissues.

Blinding the study for anakinra is a difficult procedure because of the occurrence of local skin reactions in a significant amount of patients. To maintain the double-blind design of this trial, side effects will be evaluated by an independent PA. In earlier “double blind” trials, medication was injected in the presence of the main investigator [27]. The effect of anakinra will be measured up to 6 months after the start of treatment. In this manner, we can evaluate the long-term effect of blocking IL-1 for a short period. It will provide more insight into the best treatment for CFS patients when blocking IL-1 appears to be effective.

In conclusion, this study will provide more insight into the pathophysiology and treatment of patients with CFS. If an effective treatment can be found, this will drastically improve the quality of life in patients with this disabling disease.

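### The stated rule for adverse events is passive, and the article describes no uniform question put to both arms in a trial that it says is hard to blind

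*Protocol article*

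**What the plan says.** The Adverse events section gives a broad definition, "any undesirable experience occurring to a subject during the study, whether or not considered related to the investigational product", and then a rule for capture: "All adverse events reported spontaneously by the subject or observed by the investigator or his staff will be recorded".

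The section on study medication, randomization and follow-up adds three elements:

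- Patients inject at home: "Medication is used once daily, during a period of 4 weeks". They are told to bring adverse effects to the PA rather than to the research physician. The PA passes side effects to an independent physician, who can examine the patient and stop treatment.
- The research physician and the principal investigator are kept unaware of side effects, because local skin reactions make the anakinra arm hard to blind.
- There is one call on treatment: "After 1 week, patients will be contacted by telephone to evaluate the occurrence of any problems regarding the use of medication". Visits follow at week 4 and, if needed, at 6 months. An extra visit to the independent physician is possible for serious side effects.

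On the fatigue scale (CIS), the Outcome measures section says: "Patients will fill out this web-based questionnaire weekly during the course of the trial". The pain scale (VAS) is completed with it. The Statistical analysis section says nothing about adverse events.

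**The concern.** Passive capture finds what the patient thinks worth mentioning or what staff happen to see. Two features of this trial make that weaker than usual.

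First, the article itself says that skin reactions threaten the blind. A patient who has worked out that she receives active drug may report more readily, and one who believes that she has placebo may report less. A difference between arms could then reflect belief as well as incidence.

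Second, the instruction to patients concerns adverse effects, and the week-1 call concerns use of the medication. Both are narrower than the definition, which includes events unrelated to the product. A patient who takes an infection for an ordinary cold has no described prompt to mention it, yet infection is one of the risks that the Adverse events section discusses.

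The abstract says that the trial will assess the clinical usefulness of anakinra. That judgement needs a fair comparison of harms as well as of fatigue, and no later analysis plan can recover events that nobody asked about.

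**Working it through.** No arithmetic settles this. The documents state no adverse-event rate, no expected difference and no adverse-event analysis, so there is no figure to reproduce. The check is to set each described route beside the definition and ask whether it puts a uniform question about all adverse events to both arms.

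1. **Spontaneous report (Adverse events).** The scope is all events, but the patient must start the report. Not a uniform enquiry.
2. **Observation by the investigator or staff (Adverse events).** Injections are done at home, and the described visits during the first 4 weeks are at weeks 0 and 4. The principal investigator and research physician are deliberately kept uninformed, so this half of the rule falls mainly to the PA and the independent physician. The two sections should be reconciled on who observes and records.
3. **Instruction to report to the PA (Study medication).** This names a recipient and applies to every patient. It still depends on the patient coming forward, and it refers to adverse effects, which invites her to judge causation first. Not a uniform enquiry about all events.
4. **Week-1 call (Study medication).** This is a real prompt, made to every patient. It happens once and its stated subject is the use of the medication. It may draw out some events, but its described scope is narrower than the definition.
5. **Week-4 visit (Study medication).** A contact at the end of treatment, with adherence evaluated and syringes returned. The text describes no adverse-event question there. Fig. 1, which lists the procedures, is not shown, so one may exist.
6. **Extra visit for serious side effects (Study medication).** It is triggered by an event already known, so it does not help to find events.

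None of the six, as described in the text, is a fixed question on all adverse events asked of everyone. Routes 3 and 4 reduce the gap without closing it.

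The direction of any bias is not determined. Belief in active treatment could raise reporting in the anakinra arm, while unprompted capture could lose events in both arms.

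**The case against.** The strongest reply is that the rule is less bare than it looks. Every patient is told to whom she should report. The PA and the independent physician are not shielded from side effects. The week-1 call is a scheduled prompt, and a week-4 visit closes the treatment period. A journal article also commonly leaves case-report forms and interview prompts to the full protocol. Much of this stands. It would be wrong to say that nothing is asked during treatment, or that nobody is placed to observe. What remains is that the article does state a capture rule, that the rule is passive, and that no other described route matches the breadth of its own definition.

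A second reply is that a prompted question is also answered in the light of what the patient believes. That is true. A uniform question reduces differences in whether an event is mentioned at all, but it does not remove belief from the answer.

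A reader might also infer a stronger point. The definition covers the whole study, drug is given for 4 weeks, and follow-up then runs on "to evaluate if the expected effects of the medication are maintained during the follow-up period of 5 months". It is tempting to conclude that harms are counted over 6 months and so diluted by off-drug time. The documents do not support this. They set a window for defining and recording events, and state no count, denominator or comparison period. A table limited to the treatment weeks remains possible if onset dates are kept. At most, an on-drug excess would be diluted if events were pooled over the whole study, and nothing says that they will be.

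**Conclusion.** The point holds in a limited form. As written, the capture rule is passive, and the other routes described do not add a uniform enquiry about all adverse events. In a trial whose blind is acknowledged to be fragile, following the rule literally gives a harm comparison that is less complete and more dependent on patients' beliefs than it need be. In addition, the reliance on observation by the investigator does not fit well with keeping the principal investigator uninformed.

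The size cannot be stated, because the documents give no rate from which to derive it. The conclusion assumes that the procedures figure and the full protocol contain no standard adverse-event question. If they do, only the mismatch in wording remains. This is a cheap improvement and does not affect the primary fatigue analysis.

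**What to change.** - At the existing week-4 visit, have the PA ask every patient one fixed, open question about any new complaint since the first injection, with onset and stop dates, covering weeks 0-4. Ask it only after the week-4 CIS and VAS have been submitted.
- Have the PA use the same neutral wording at the existing week-1 call.
- Send the answers only to the PA and the independent physician, so that the present shielding of the research physician and principal investigator is kept.
- Reword the Adverse events section so that it names the same reporting route as the study medication section and says who observes and records.
- Tabulate events with onset in weeks 0-4 by arm, separately from those in off-drug follow-up.

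An item on the weekly web form would be simpler, but it is not advised. Prompts in weeks 1-3 would come before the week-4 CIS, which is the primary endpoint, and could draw attention to skin reactions and to guessing the arm. The week-1 question also precedes that endpoint. It is one neutral question at a call that already asks about problems, so it should add little.

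The cost is more mild events to record, slightly longer contacts and one additional table. No new visit is needed.

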### Statistical analysis

The primary analysis will be the comparison between the two different treatment groups (anakinra or placebo) at 4 weeks. Data will be analyzed on an ITT basis. Missing values will be replaced using multiple imputation with fully conditional specification with at least five imputations. The imputation method that will be used is predictive mean matching for missing data in primary and secondary outcome measures. Aside from condition, we will use the following variables assessed at baseline to generate the imputations: duration of symptoms, age, BMI and baseline values of the outcome measures.

The results will be analyzed with SPSS for Windows. To determine if there is a significant difference between the intervention arm and placebo condition, ANCOVA will be used with the outcome measure on the second assessment as the dependent measure, the baseline score as the covariate, and condition as the fixed factor [39]. We will test if significant differences exist between both groups in mean age and BMI at baseline, both known to influence circulating cytokine levels. If so, these variables will be entered as covariates in the ANCOVA. When a statistically significant difference is found in the primary analysis, a sensitivity analysis will be performed on the basis of different assumptions about the values of missing data. For the secondary outcome measures, the same analysis will be repeated, but the secondary outcome measures at the second assessment will serve as the dependent variable and the scores at baseline as the covariate.

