### Power calculation

The sample size is based on the fatigue subscale score of the CIS at 4 weeks. In the present study, the power calculation is based on results from comparable studies with CFS patients where fatigue severity was determined with the CIS-fatigue scale [40]. If interleukin-1 plays a central role in CFS symptomatology, we expect a considerable reduction of fatigue following treatment. Assuming a large controlled effect size of 0.85, an alpha of 0.05 and a power of 0.80, 23 patients are needed in each arm of the study. The number of patients can be further reduced by using ANCOVA, with the outcome measure on the second assessment as the dependent measure, the baseline score as the covariate, and condition as the fixed factor. In this kind of trials, ANCOVA yields greater power compared to other statistical methods [39]. Based on the correlation between the pre- and post CIS fatigue scale, the sample size of 23 can be multiplied by 0.883 (1 to 0.342^2^). Including an assumed dropout rate of 20 percent, we will have to include 25 patients in each group to demonstrate a significant difference between the medication group and placebo.

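### The listed imputation predictors for week-4 CIS omit the weekly on-treatment CIS scores; this loses precision and, if dropout follows early fatigue, biases the treatment difference in a direction that cannot be known in advance

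*Protocol article*

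**What the plan says.** All references are to the protocol article. Under Statistical analysis: "Missing values will be replaced using multiple imputation with fully conditional specification with at least five imputations". The next sentence sets the technique and its targets: "The imputation method that will be used is predictive mean matching for missing data in primary and secondary outcome measures". The predictors follow: "Aside from condition, we will use the following variables assessed at baseline to generate the imputations: duration of symptoms, age, BMI and baseline values" (that is, each outcome's own starting score). Every named variable other than condition is a baseline variable.

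Under Outcome measures, for the CIS: "Patients will fill out this web-based questionnaire weekly during the course of the trial and monthly during the follow-up period". Under Secondary outcome measures: "Only the VAS pain scale will be filled in weekly (together with the CIS) during the trial".

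The Power calculation gives a pre-post CIS correlation of 0.342 and reaches 25 per arm, "Including an assumed dropout rate of 20 percent". The analysis is an ANCOVA of the week-4 score on baseline score and condition.

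Two other provisions bear on the point. The section on withdrawal promises attempts to keep measuring patients who discontinue. Statistical analysis adds a sensitivity analysis under other missing-data assumptions, to be run if the primary result is significant.

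**The concern.** A patient lost before week 4 will often have left one, two or three weekly scores on the primary instrument itself. The listed model does not use them. It imputes her week-4 value from her arm and her baseline, so she is treated much like a completer of that arm with a similar baseline, whatever her weekly scores showed.

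Two things are at stake. Information already paid for is discarded in a trial sized close to its 80% power target. And the missing-at-random assumption is made conditional on condition and baseline only. If leaving depends on how fatigued the patient was during treatment, that assumption fails although the data that would repair it are in hand.

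This is not a detail left to a later document: the protocol names the method, the technique and the predictors.

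**Working it through.** **1. The plan's own figures.** A two-sided t-test with d = 0.85, alpha 0.05 and power 0.80 needs 22.73, so 23 per arm, as stated (two-sided is assumed). The ANCOVA factor is 1 − 0.342² = 0.883, and 23 × 0.883 = 20.3. Then 20.3 × 1.2 = 24.4 gives the stated 25; 20.3 / 0.8 = 25.4 would give 26, a difference not pursued here. With 20% dropout, 25 × 0.8 = 20 complete per arm, about 40 in all.

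**2. What baseline can recover.** 0.342² = 0.117, so about 12% of week-4 variance.

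**3. Simulation inputs.** From the protocol: baseline correlation 0.342, true difference −0.85 SD (negative favours anakinra), 20% missing, 25 per arm. Assumed, because the document gives no figure: correlation of the last weekly score with week 4 of 0.5 to 0.85; 75% of the effect present at that visit; where dropout is informative, log-odds of 1.5 per SD of the weekly score. The listed model is represented by condition plus baseline CIS.

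**4. Large-sample bias in the difference** (N = 400,000, regression imputation):

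| Who drops out | Corr. 0.5 | 0.7 | 0.85 |
|---|---|---|---|
| Random | 0.000 | −0.001 | +0.002 |
| Poor responders, both arms | +0.047 | +0.070 | +0.087 |
| Poor responders, anakinra only | −0.100 | −0.155 | −0.196 |
| Poor responders, placebo only | +0.097 | +0.157 | +0.198 |
| Poor responders on placebo, good responders on anakinra | +0.174 | +0.274 | +0.347 |

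Positive values point towards no effect. With the weekly score added, the bias is at most 0.007 in absolute value in every cell.

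The mechanism shows in the anakinra-only row at 0.7: 24% of that arm is missing and its mean is 0.155 too low, so the dropouts are imputed about 0.155 / 0.24 = 0.65 SD less fatigued than they are. When the same mechanism acts in both arms, the arm biases (−0.169 placebo, −0.100 anakinra) largely cancel: −0.100 + 0.169 = +0.069.

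**5. At 25 per arm** (predictive mean matching, 10 imputations, Rubin pooling, 1,500 runs, correlation 0.7 unless stated):

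| Scenario | Listed: mean / SE / power | With weekly score |
|---|---|---|
| Random | −0.835 / 0.304 / 0.760 | −0.831 / 0.285 / 0.814 |
| Random, corr. 0.85 | −0.835 / 0.299 / 0.764 | −0.836 / 0.273 / 0.849 |
| Poor, both arms | −0.759 / 0.295 / 0.711 | −0.790 / 0.279 / 0.776 |
| Poor, placebo only | −0.673 / 0.304 / 0.597 | −0.780 / 0.281 / 0.767 |
| Opposite in the two arms | −0.547 / 0.305 / 0.452 | −0.741 / 0.290 / 0.728 |

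The Monte Carlo error of a power near 0.76 is √(0.76 × 0.24 / 1,500) = 0.011.

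For scale, the approximate ANCOVA SE is √(0.883 × 2/25) = 0.266 with complete data and √(0.883 × 2/20) = 0.297 with completers only. Under random dropout the listed model (0.304) therefore recovers essentially nothing beyond the completers. The weekly score recovers about half of the loss: (0.304 − 0.285) / (0.304 − 0.266) = 0.5.

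**6. Type I error, listed predictors.** Same mechanism in both arms: 4.9% (1,000 runs, bias −0.006). Anakinra only: 9.0% in those runs, and 6.9 to 8.6% in a further set with 29% v 9% missing, falling to 4.4 to 5.0% with weekly scores. Opposite patterns, the most extreme case tried: 14.5%, falling to 4.3%.

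**7. Bias left after the change.** From the table, −0.780 leaves 0.07 and −0.741 leaves 0.11. The separate 1,000 runs left 0.074 (both arms) and 0.077 (placebo only).

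**The case against.** **The text may not exclude weekly scores.** Fully conditional specification lets incomplete variables predict one another, and weekly CIS and VAS are repeated measurements of outcomes to be imputed. The sentence could be read as naming only the baseline part of the model. That reading is possible, but the sentence sets out what generates the imputations and no post-baseline score is there. Most other outcomes are measured only at baseline and week 4 during treatment and would tend to be missing together with the CIS.

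**Safeguards exist.** The CIS is web-based, and efforts are made to continue measurements, so stopping treatment need not mean a missing week-4 score. A significant result triggers a sensitivity analysis, which is when an inflated effect would matter most. Both reduce the problem. Neither changes the primary estimate, and the second does nothing for a missed effect.

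**The size rests on assumptions.** The weekly correlation and the dropout mechanism are not in the document. With ten uninformative predictors added, to mimic the longer baseline list, power under random dropout went from 73% to 78%, so a gain of about five points persists.

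**Stronger readings that do not hold.** A reader might infer that the bias probably favours anakinra. Only poor responders leaving the anakinra arm gave that; the same mechanism in both arms, or on placebo alone, works against the drug. The anakinra-specific problem that the protocol describes is injection-site reactions, and nothing links these to early fatigue scores. A reader might also infer a general inflation of type I error, but there was none when the mechanism was the same in both arms. Nor does the change remove all bias under predictive mean matching at this sample size.

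**Conclusion.** The point holds as a weakness in a stated model that can be improved at almost no cost. The precision loss needs no adverse mechanism: about 5 to 7 power points under 20% random dropout at an assumed correlation of 0.7, from about 0.75 to 0.81–0.82, which straddles the planned 0.80.

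The bias is conditional on dropout following early on-treatment fatigue. It is about 0.05 to 0.10 SD towards no effect if the mechanism is shared by the arms, and about 0.1 to 0.2 SD in either direction if it acts in one arm. Type I error is affected only if the mechanism differs by arm. The documents do not say which pattern to expect, so no direction should be claimed. A patient lost before her first weekly score gains nothing from the change.

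**What to change.** State in the analysis plan, before unblinding, that the imputation model for week-4 CIS includes the post-baseline weekly CIS scores as well as condition and baseline CIS. Add the weekly VAS scores to the model for VAS pain, and the monthly follow-up CIS to the 6-month CIS imputation. Keep the other predictors to the few relevant to each outcome, so that the model stays estimable with about 40 completers.

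The cost is a few lines of text and some variables in the imputation call; no new data are needed. The downside is a slightly larger imputation model. Residual bias of up to about 0.08 SD can remain when the mechanism is shared or acts in one arm, and about 0.11 SD in the opposite-pattern case, so the sensitivity analysis is still needed.

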### Study medication, randomization and follow-up

Eligibility for participation of patients is determined at the pre-study visit. After giving informed consent, patients will be screened for inclusion and exclusion criteria by means of the examinations listed in Fig. 1. Laboratory investigations performed earlier will be evaluated for all patients and will be repeated if not performed recently, or when essential measurements, as recommended by others [31], are missing. Patients who qualify to be included will be randomized 1:1 to receive either anakinra (100 mg/day) or placebo. Randomization will be performed by the study pharmacist (Department of Clinical Pharmacology, Radboud University Medical Center), will be known only by the pharmacist and will be exposed only in case of emergency. If the code is broken, it will render the participant not eligible. When the study is completed, the randomization list will be made available by the study pharmacist.

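### Age and BMI enter the ANCOVA, including the primary CIS model, only if a baseline significance test is positive, so the primary model is not fixed in advance

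*Protocol article*

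**What the plan says.** The Statistical analysis section defines the comparison of arms at week 4: "ANCOVA will be used with the outcome measure on the second assessment as the dependent measure, the baseline score as the covariate", with treatment condition as the fixed factor. It then adds a conditional step: "We will test if significant differences exist between both groups in mean age and BMI at baseline, both known to influence circulating cytokine levels". A positive result changes the model: "If so, these variables will be entered as covariates in the ANCOVA". The same analysis is to be repeated for the secondary outcomes, so the rule carries over to them.

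The level of the baseline tests is not given. It is also unclear whether one positive test brings in one covariate or both.

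Three other places bear on the point:
- The section on outcome measures states: "The primary outcome measure is fatigue severity measured with the subscale fatigue severity of the Checklist of Individual Strength (CIS) at 4 weeks". It is therefore a fatigue score, not a cytokine level.
- Power calculation: the ANCOVA is described with "the baseline score as the covariate, and condition as the fixed factor". Age and BMI do not appear.
- Statistical analysis, on missing data: age and BMI are used in the imputation model unconditionally.

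Nothing in the article fixes age or BMI as covariates in advance, or limits the rule to the cytokine outcomes.

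**The concern.** Allocation is randomized 1:1, so any difference in mean age or BMI between arms arises by chance. A test of that difference asks whether randomization produced an unusual split. It does not ask whether the covariate predicts week-4 fatigue, and that is what makes adjustment worthwhile. A strongly prognostic covariate is left out in most trials because its arms happen to look similar, while an irrelevant one is brought in when they do not.

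The consequence is that the article does not commit to one primary model. Up to four covariate sets are possible: baseline score alone, plus age, plus BMI, or plus both. In a 50-patient trial with one primary test, a borderline result could be significant under one set and not under another, and which set counts would have been settled by chance. If age or BMI does predict fatigue, the rule also gives up most of the power that planned adjustment would bring.

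**Working it through.** **Inputs from the protocol article.** Effect size 0.85, alpha 0.05, power 0.80, 23 per arm; correlation of baseline with week-4 CIS 0.342; 20% dropout; 25 per arm (Power calculation).

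**Assumptions, because the article gives no figures.** Baseline tests at two-sided 0.05; age and BMI independent of each other; each correlated with week-4 CIS at 0 to 0.5. In the table, only the covariate with a positive test enters.

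**Step 1: the plan's own figure.** The article states: "Assuming a large controlled effect size of 0.85, an alpha of 0.05 and a power of 0.80, 23 patients are needed in each arm". A two-sided t-test needs 22.73, so 23 per arm (power 0.805). Then "the sample size of 23 can be multiplied by 0.883": 1 − 0.342² = 0.883, and 23 × 0.883 = 20.3. Allowing for 20% dropout, 20.3 / 0.8 = 25.4, against 25 stated, and 20 / 0.8 = 25. The figure reproduces, and its variance factor uses the baseline score only.

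**Step 2: how often chance changes the model.** P(at least one positive test) = 1 − 0.95² = 0.0975; simulated 0.0974. If age and BMI are correlated, this falls towards 0.05.

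**Step 3: what follows.** Simulation with 25 per arm and 100,000 trials per setting, comparing baseline score only (B), the test-then-adjust rule (R), and always adjusting for age and BMI (A):

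| Correlation of each covariate with CIS | Type I error B / R / A | Power at 0.85 B / R / A | Verdict differs B vs R, among trials where the rule triggers: no effect; 0.85 |
|---|---|---|---|
| 0 | 0.049 / 0.049 / 0.050 | 0.875 / 0.871 / 0.859 | 2.9%; 7.0% |
| 0.2 | 0.050 / 0.048 / 0.050 | 0.875 / 0.875 / 0.890 | 6.0%; 10.9% |
| 0.3 | 0.049 / 0.045 / 0.050 | 0.875 / 0.880 / 0.925 | 9.3%; 15.3% |
| 0.5 | 0.050 / 0.036 / 0.050 | 0.875 / 0.894 / 0.996 | 18.7%; 24.6% |

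**Step 4: put the verdict changes on all trials.** The last column applies only to the 9.74% of trials where the rule triggers. Multiplying through:
- Correlation 0, no effect: 0.0974 × 0.0288 = 0.3%.
- Correlation 0.3, effect 0.85: 0.0974 × 0.1531 = 1.5%.
- Correlation 0.5, effect 0.85: 0.0974 × 0.2457 = 2.4%, an extreme case.

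A separate simulation over correlations 0 to 0.4 gives about 0.4% to 3.3% of all trials. The upper end needs an effect of 0.6, which is not in the article; at 0.85 the maximum is about 2%.

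**Step 5: validity and power.** In that simulation, 95% confidence intervals under the rule covered in 95% to 96% of trials. Type I error was 0.053 at correlation 0 (simulation error; the larger run gives 0.049), falling to 0.040 at correlation 0.4. At correlation 0.3 and effect 0.6, power was 0.59 with the baseline score only, 0.59 under the rule and 0.67 with fixed adjustment.

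**Step 6: cost of fixed adjustment when the covariates do nothing.** At correlation 0 and effect 0.85, power is 0.859 against 0.871 under the rule (1.2 points) and 0.875 with the baseline score only (1.6 points). With 20 analysed per arm it is 0.760 against 0.779 under the rule (1.9 points).

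**The case against.** The best defence is that the choice is bounded. The two candidate covariates, the trigger and the action are written down, and the allocation is known only to the pharmacist until the study ends. This stands: it is not open-ended selection by an analyst who has seen the results.

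A reader might infer that the rule inflates false positives, or that the reported interval is too narrow because it ignores the model choice. The calculations do not support either. Type I error stays at or below about 0.05 apart from simulation error, and coverage is 95% to 96%.

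A reader might also take the verdict changes of up to a quarter in the table as the trial's risk. They hold only within the roughly one trial in ten where the rule triggers. Nor is a changed verdict in itself an error: when an imbalanced covariate is prognostic, the adjusted result is the better one.

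Two further inferences are too strong. Sizing the trial on baseline score and condition does not contradict the analysis section, because sample sizes are often based on the simplest model. The stated reason, that age and BMI influence cytokines, is not incoherent for a fatigue outcome either, since the trial's premise is that IL-1 drives fatigue. It is only an indirect reason, and it argues for including these variables always rather than when an imbalance test is positive.

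None of this answers the central point. The article fixes a rule that leaves the primary model undetermined, and a later analysis plan that followed this text could not remove it.

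**Conclusion.** The point holds as a badly fixed model choice of modest consequence. The covariate set of the primary CIS analysis depends on a test that carries no information about whether adjustment is useful. Under the assumptions above, the model changes by chance in 9.75% of trials, and the significance verdict in about 0.4% to 3.3% of all trials (at most about 2% at the planned effect size, for correlations 0 to 0.4).

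The harm is not invalid inference. It is an unfixed primary model, and lost power if age or BMI predicts the outcome: at correlation 0.3 each, 0.88 against 0.92 at effect 0.85, and 0.59 against 0.67 at effect 0.6. That the rule exists is certain from the text. The size of its effect is a range, because the article gives neither the level of the baseline tests nor any correlation of age or BMI with fatigue.

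**What to change.** Delete the baseline significance tests. Before unblinding, prespecify one ANCOVA with arm, baseline score, age and BMI, all always included, for the primary CIS outcome and for the secondary outcomes including cytokines. Report the baseline-score-only model assumed in the Power calculation as a sensitivity analysis.

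Making baseline score only the primary model would also end the dependence on chance, but it would recover none of the lost power (0.59, the same as under the rule, at correlation 0.3 and effect 0.6).

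The change is one of wording. It needs no new patients and no new data, since age and BMI are already required for the imputation model. It costs two degrees of freedom, and about 1 to 2 points of power if neither covariate predicts the outcome.
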